### Sample size considerations

Sample size is feasibility-driven because of orphan drug conditions [21], and, in consequence, our power calculation describes under which circumstances this trial can reach an adequate power for an achievable sample size. In this study a maximum of 120 patients can be included within a reasonable time frame of 3 years of recruitment. With a 1:2 randomization, this leads to 40 patients in the doxorubicin arm and 80 patients in the pazopanib arm.

The one-sided type I error rate is set to 2.5 %. The treatment groups will be compared by using HRs. For both treatment groups, a median PFS of 6 months is assumed [8, 22]. The accrual time is 36 months, and the minimum observational time is 10 months. Under these conditions, noninferiority with a margin of 1.8 for the HR can be concluded with a power of >80 %. An anticipated rate of dropout and exclusion from the primary analysis population of 10 % maintains a power of 79–80 %.

### Statistical analysis

#### Primary analysis

The primary analysis will be performed on the per-protocol (PP) population and, as a sensitivity analysis, on the intention-to-treat (ITT) population. Consistency between results in ITT and PP analysis is needed to draw any conclusion regarding differences in PFS. The PP population will include all randomized patients who received the assigned study treatment and took the study medication according to the protocol (allowing for dose reduction and/or temporary interruption, or termination of trial drug intake without other anticancer therapy being initiated before documented progression). If patients start another anticancer therapy, they will be censored at the respective time point in the ITT analysis.

For PFS, a Cox regression model will be used to calculate the HR of pazopanib/doxorubicin and the respective two-sided 95 % CI. If the upper limit of this CI in the PP population is less than 1.8, noninferiority will be concluded. The Cox regression model is adjusted for ECOG score (0–1 vs. 2) and liposarcoma histology (yes vs. no). Kaplan-Meier curves will be drawn.

#### Secondary and safety analyses

If statistical significance is reached for the primary endpoint, a confirmatory analysis of the key secondary endpoints grade 4 neutropenia and febrile neutropenia will be performed in hierarchical order. If no statistically significant difference for grade 4 neutropenia is observed, febrile neutropenia will be considered descriptively. The rates of grade 4 neutropenia will be analyzed with a Poisson regression model adjusted for ECOG score and liposarcoma histology and allowing for clustering of the outcome within patients by using a random effects term. Superiority of pazopanib will be concluded if the upper boundary of the two-sided 95 % CI for the rate ratio (pazopanib/doxorubicin) is below 1. Rates of febrile neutropenia will be analyzed with the same approach. Due to the hierarchical order in confirmatory testing, no adjustment for multiplicity has to be done.

For the analysis of overall survival, Kaplan-Meier curves and Cox regression will be used. For analysis of PFRs after 12 and 26 weeks, a logistic regression model will be used to calculate the OR between the two treatment groups. Corresponding two-sided 95 % CIs will be calculated. The objective tumor response rate will be computed with 95 % CIs in each treatment arm. Patients with progression, early death, or unknown status are considered as failures. Time to onset of response will be reported as median and range. Occurrence and frequency of AEs and serious AEs will be evaluated separately for both treatment groups, and frequency tables and corresponding 95 % CIs will be shown.

The key secondary analyses and analyses of all further efficacy endpoints will be conducted on the ITT population with sensitivity analyses based on the PP population. Analysis of safety endpoints will be conducted on the full analysis set. No interim analyses are planned in this trial.

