### Study design

This trial is a randomized, open-label, multicenter, phase II noninferiority study designed to compare pazopanib with doxorubicin as first-line treatment in elderly patients with metastatic or advanced STS. A total of 120 patients from 13 (German and Belgian) study centers will be enrolled, comprising 40 patients in the doxorubicin arm and 80 patients who will receive pazopanib.

The overall study duration will be approximately 50 months, including a recruitment period of 36 months, a 4.5-month period of treatment with doxorubicin (18 weeks) or pazopanib until treatment failure, and follow-up of at least 10 months.

Baseline and follow-up assessments are performed according to a predefined schedule (see Fig. 1 and Additional file 1: Figure S1). Follow-up visits occur at the same time points for both treatment arms. In both treatment groups, an end-of-treatment visit 4 weeks after the end of treatment is performed. Tumor images obtained by performing computed tomography or magnetic resonance imaging for evaluation of response and progress are taken every 6–7 weeks in the first 6 months and every 12 weeks after week 26 until progression. The Standard Protocol Items: Recommendations for Interventional Trials (SPIRIT) checklist and assessment figure of the trial can be found in Additional file 2: Table S1 and Additional file 1: Figure S1.

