#### Secondary endpoints

Key secondary outcomes are the rates of grade 4 neutropenia and of febrile neutropenia. Rates are defined as the number of scheduled examinations where grade 4 neutropenia is diagnosed (febrile neutropenia respectively) divided by the follow-up time until progression, death, or the end of the study, or (in case of treatment switch) until initiation of another anticancer treatment. Incident diagnoses will be considered at the next examination. In addition to the primary outcome, PFRs after 12 and 26 weeks from the date of randomization and overall survival, defined as time from randomization to death due to any cause, will be estimated. Further secondary endpoints are objective tumor response, calculated as objective response rate, along with time to onset of response. Assessment of response and progression is based on Response Evaluation Criteria in Solid Tumors version 1.1, without independent review of tumor response or progression events.

Safety and tolerability will be assessed continuously throughout the course of the study. Toxic and side effects are evaluated by using the National Cancer Institute Common Terminology Criteria for Adverse Events version 4.0. Quality of life is measured with the European Organisation for Research and Treatment of Cancer (EORTC) 30-item core quality of life questionnaire (the QLQ-C30). Geriatric assessments are made according to the EORTC Elderly Task Force guidelines.

The predictive role of biomarkers will be assessed to predict the PFS rate at 26 weeks after the start of treatment. Biomarkers measured in the study will include placental growth factor, fibroblast growth factor, VEGF, PDGF, angiopoietin 2, and interleukin 8. Blood samples will be taken at baseline, at 2 weeks, and at each scheduled follow-up visit starting from 3 weeks after randomization.

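### The 12- and 26-week progression-free rates are compared by logistic regression, which has no place for patients censored before the landmark; a Kaplan-Meier-based comparison would avoid this (minor)

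*Protocol article*

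**What the plan says.** All references are to the protocol article.

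- **Secondary endpoints:** the article will estimate "PFRs after 12 and 26 weeks from the date of randomization", alongside overall survival.
- **Secondary and safety analyses:** for these rates, "a logistic regression model will be used to calculate the OR between the two treatment groups", with two-sided 95% CIs. Efficacy endpoints of this kind are analysed on the ITT population, with the per-protocol population as sensitivity analysis.
- **Same section, directly after the sentence on objective response rate:** "Patients with progression, early death, or unknown status are considered as failures". The text does not say whether this also covers the progression-free rates.
- **Primary analysis:** if patients start another anticancer therapy, "they will be censored at the respective time point in the ITT analysis". PFS is analysed by Cox regression, and Kaplan-Meier curves are planned.
- **Sample size considerations:** median PFS of 6 months in both arms, at least 10 months of observation, and 10% for dropout and exclusion from the primary analysis population combined.

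**The concern.** A progression-free rate at a fixed week is one point on the PFS curve. Logistic regression needs a status for every patient at that week, and a patient censored earlier has none. Excluding such patients, counting them as failures and counting them as progression-free are three different estimators. In general none of them equals the Kaplan-Meier value from the same data, so one report could carry two disagreeing 26-week rates.

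The sentence on unknown status does not settle this. If it covers response only, the article states no rule for the progression-free rates. If it covers them too, patients whom the PFS analysis censors count here as progressed, which lowers the rate.

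The rates are not key secondary endpoints, but they are not idle either. The Discussion says that estimates and confidence limits for PFS rates, as well as for the hazard ratio, will receive particular attention in the interpretation. The odds ratio is also exposed to unequal censoring. Doxorubicin ends after six three-week cycles (18 weeks), while pazopanib continues, so between weeks 18 and 26 only one arm is off treatment by design, and new therapy could start at different rates in the two arms.

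**Working it through.** **1. The plan's own figure.** The article gives no figure for the two rates, so its assumptions were checked on the stated power. With L = ln2/6 per month, uniform accrual over 36 months and 10 months' minimum follow-up:

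P(event) = 1 − (e^(−10L) − e^(−46L))/(36L) = 0.925.

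Power (Schoenfeld) = Φ(√(d × 1/3 × 2/3) × ln 1.8 − 1.96).

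- 120 patients: d = 111.1 events, power 83.1% (stated: above 80%).
- 108 patients, after 10% loss: d = 99.9 events, power 79.1% (stated: 79–80%).

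Both reproduce, so exponential PFS with a 6-month median is a fair reading of the plan.

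**2. True landmark rates.** Six months is 26.09 weeks, so λ = ln2/26.09 = 0.02657 per week and S(t) = e^(−λt). This gives S(12) = 72.7% and S(26) = 50.1%. A Kaplan-Meier estimate targets these values whatever the amount of independent dropout.

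**3. Binary coding with dropout.** Assume independent exponential dropout with hazard μ, set so that 1 − e^(−26μ) equals the assumed dropout by week 26. For 10%, μ = 0.00405 per week. At time t:

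- known progression-free: pf = e^(−(λ+μ)t)
- event seen: ev = λ/(λ+μ) × (1 − pf)
- unknown: un = μ/(λ+μ) × (1 − pf)

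At week 26 with 10% dropout, pf = 0.451, ev = 0.476 and un = 0.073. The three codings give:

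- unknown = failure: pf = 45.1%
- excluded: pf/(pf + ev) = 0.451/0.927 = 48.6%
- unknown = progression-free: pf + un = 52.4%

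| Dropout by week 26 (assumed) | Week | Failure | Excluded | Progression-free | True |
|---|---|---|---|---|---|
| 5% | 26 | 47.6% | 49.4% | 51.2% | 50.1% |
| 10% | 12 | 69.2% | 72.2% | 73.3% | 72.7% |
| 10% | 26 | 45.1% | 48.6% | 52.4% | 50.1% |
| 20% | 26 | 40.1% | 47.0% | 54.7% | 50.1% |

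**4. Effect on the odds ratio.** With equal dropout and equal true PFS, both arms shift alike and the odds ratio stays at 1. Take instead equal true PFS but dropout of 5% in one arm and 20% in the other. This imbalance is purely an assumption. The odds ratio at week 26, lower-dropout arm over higher, is:

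- failure: (0.476/0.524)/(0.401/0.599) = 1.36
- excluded: (0.494/0.506)/(0.470/0.530) = 1.10
- progression-free: (0.512/0.488)/(0.547/0.453) = 0.87

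Under that imbalance, even the direction depends on the coding.

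**5. Scale of the noise.** The standard error of a 50% rate is √(0.25/80) = 5.6 points in the pazopanib arm and √(0.25/40) = 7.9 points in the doxorubicin arm. The 95% CI for an odds ratio at week 26 runs a factor of e^(1.96 × √(1/10 + 1/20)) = 2.14 either side of the estimate.

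**The case against.** The strongest reply is that the effect is small and the endpoint minor. Much of that stands.

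- The 10% in the sample size section includes exclusions from the primary analysis population, which is the per-protocol set, whereas these rates use ITT. True dropout should be lower.
- With at least 10 months of observation there is no administrative censoring before week 26, and treatment failure is itself a PFS event. Both limit the number of unknowns.
- Even at 10% the error at week 26 is −5.0 to +2.3 points, and simple exclusion is off by only 1.5 points. Each is below one standard error in either arm.
- The rates are outside the testing hierarchy, and censoring-aware rates can be read from the planned curves.
- The coding of unknowns could be set out in an analysis plan that is not shown. That would fix which coding applies; it would not let a logistic model use a censored patient.

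A reader might infer two stronger points, and the documents support neither.

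*Scan timing.* Scans "every 6–7 weeks in the first 6 months and every 12 weeks after week 26 until progression" might seem to put the landmarks at the mercy of when the last scan fell. But the same words fit a fixed grid at weeks 6, 12, 19 and 26 (gaps of 6, 6, 7 and 7 weeks), which lands on both landmarks, and the schedule figure is not shown. The article also states "Follow-up visits occur at the same time points for both treatment arms", so a difference in timing between arms is speculation. Kaplan-Meier would not remove a timing effect in any case, so it is no argument against logistic regression.

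*The 40% benchmark.* The Background cites a 12-week rate of 40% as a sign of activity, but for pretreated patients. This is a first-line trial, and no decision rule here uses that threshold.

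**Conclusion.** The point holds as a minor finding on the choice of method. The article fixes logistic regression for two rates that come from censored data. Under either reading of the unknown-status sentence, patients censored before the landmark are excluded or given a status that they did not have.

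For the absolute rates the error is a few points: at most 5.0 at week 26 and 3.5 at week 12, with 10% dropout taken as an upper illustration. This rests on exponential PFS with the plan's 6-month median and on independent dropout.

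For the odds ratio, bias requires censoring that differs by arm. The treatment durations make this plausible, but the article reports no dropout by arm, so the range of 0.87 to 1.36 illustrates what could happen and does not estimate it. The analysis also assumes that the rule of censoring at new therapy, stated for the ITT PFS analysis, carries over to rates taken from the same endpoint.

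The primary Cox analysis, its margin and its power are untouched.

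**What to change.** Estimate the 12- and 26-week rates from the Kaplan-Meier curve of PFS in the ITT population, by arm with 95% CI, under the same censoring rule as the ITT PFS analysis. Compare the arms by the difference in rates with a two-sided 95% CI. If adjustment is wanted, use pseudo-value regression with ECOG score and liposarcoma histology as covariates. Repeat in the per-protocol population as already planned. Keep the logistic odds ratio at most as a sensitivity analysis, and say there how patients of unknown status are coded. State also whether the sentence on unknown status applies to objective response only.

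The cost is wording in the analysis plan, with no new data; the Trial status section reports follow-up as ongoing. There are two downsides. A rate difference replaces the odds ratio as the main summary, and the method assumes non-informative censoring, as the Cox analysis already does.

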## Methods

### Study objectives

The primary aim of this study is to show that PFS in the pazopanib group is not inferior to PFS in the doxorubicin group. Key secondary objectives are to show superiority of pazopanib compared with doxorubicin regarding neutropenia grade 4 and/or febrile neutropenia. Further secondary objectives are to analyze treatment effects on overall survival, objective tumor response, time to onset of response, quality of life, safety, and tolerability, as well as to investigate predictive biomarkers.

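### The plan aims at treatment effects on response and on time to onset of response, but its stated analyses give no between-arm estimate for either

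*Protocol article*

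**What the plan says.** All references are to the protocol article.

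- Study objectives: "Further secondary objectives are to analyze treatment effects on overall survival, objective tumor response, time to onset of response", followed by quality of life, safety and tolerability.
- Secondary endpoints: "Further secondary endpoints are objective tumor response, calculated as objective response rate, along with time to onset of response". No time origin, at-risk set or rule for patients who never respond is given for onset.
- Secondary and safety analyses, response: "The objective tumor response rate will be computed with 95 % CIs in each treatment arm". The failure rule follows: "Patients with progression, early death, or unknown status are considered as failures".
- Same section, onset: "Time to onset of response will be reported as median and range".
- Same paragraph, other endpoints: "For the analysis of overall survival, Kaplan-Meier curves and Cox regression will be used", and for the progression-free rates at 12 and 26 weeks "a logistic regression model will be used to calculate the OR between the two treatment groups".
- Same section, population: "The key secondary analyses and analyses of all further efficacy endpoints will be conducted on the ITT population", with per-protocol sensitivity analyses.

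**The concern.** The objective is comparative, but the analysis written down for these two endpoints is descriptive. If it is followed exactly, the report will contain no estimate of the effect on response and none on onset.

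For response, readers would be left to judge two intervals by eye, and overlapping per-arm intervals do not show the absence of a difference. For onset, a median and a range need observed response times, so the summary would most naturally cover responders only. Responders are selected after randomization and can differ between arms. The word effects in the objective invites a comparison that such medians cannot support.

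This matters somewhat more here than usual. The Discussion says that conclusions will draw on the whole dataset and lean on point estimates, because the 1.8 margin is so wide. Supporting efficacy endpoints therefore need an interpretable contrast.

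**Working it through.** **1. The plan's own figures.** The article gives no design figure for response or onset. Its only design calculation is the primary power.

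- Inputs (Sample size considerations): median PFS 6 months in both arms, 36 months of accrual, at least 10 months of follow-up, 40 and 80 patients, margin 1.8, one-sided 2.5%.
- Event probability, assuming exponential PFS and uniform accrual, with λ = ln 2/6: 1 - (e^(-10λ) - e^(-46λ))/(36λ) = 0.925.
- Power = Φ(√(D × 1/3 × 2/3) × ln 1.8 - 1.96).
- 120 patients: D = 111.1, power 83.1%. With 10% lost (108 patients): D = 99.9, power 79.1%.

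Both agree with the article (above 80%, and 79-80%). Nothing below changes them.

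**2. Stated analyses side by side.**

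| Endpoint | Stated analysis | Between-arm estimate |
|---|---|---|
| Overall survival | Kaplan-Meier, Cox regression | yes |
| Progression-free rates, 12 and 26 weeks | logistic regression, OR with 95% CI | yes |
| Objective response | rate with 95% CI in each arm | none named |
| Time to onset of response | median and range | none named |

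**3. Response.** Response rates are assumed, since the article gives none. Differences are pazopanib minus doxorubicin with Newcombe 95% CIs, for 40 and 80 patients.

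| Doxorubicin | Pazopanib | Difference (95% CI), points |
|---|---|---|
| 6/40 = 15% | 12/80 = 15% | 0 (-15.4 to +12.3) |
| 8/40 = 20% | 8/80 = 10% | -10 (-25.5 to +2.8) |
| 10/40 = 25% | 8/80 = 10% | -15 (-30.9 to -1.2) |

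In the last row the exact per-arm intervals are 12.7-41.2% and 4.4-18.8%. They overlap, yet the interval for the difference excludes zero. The per-arm display does not carry the information that the contrast does.

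**4. Onset, read as a median among responders.** Take scans at weeks 6, 12, 18 and 24, in line with the 6-7 week interval in Study design. At each scan, a patient still without response or progression responds with probability r or progresses with probability g (all values assumed). The new responders at scan k are r_k × Π(1 - r_j - g), with the product over earlier scans j.

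- A: r = 0.08, 0.06, 0.05, 0.04; g = 0.20. New responders 0.0800 + 0.0432 + 0.0266 + 0.0160 = 0.166. Week 6 holds 48% of responders, so the median is week 12.
- B: every r halved; g = 0.20. New responders 0.0400 + 0.0228 + 0.0146 + 0.0091 = 0.087. Week 6 holds 46%, so the median is week 12.
- C: r as in A; g = 0.50. New responders 0.0800 + 0.0252 + 0.0092 + 0.0033 = 0.118. Week 6 holds 68%, so the median is week 6.

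From A to B the drug is half as active and the median does not move. From A to C only progression is worse, and onset looks faster.

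The direction can also reverse. Suppose 4/40 and 8/80 respond at week 6, and 9 more pazopanib patients respond at week 18. The median is week 6 on doxorubicin and week 18 on pazopanib (the 9th of 17 responders). Yet cumulative response is 10% against 10% at week 6, and 10% against 17/80 = 21% at week 18. Pazopanib is never behind.

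**5. Numbers available.** At an assumed 10-20% response there are 4-8 doxorubicin and 8-16 pazopanib responders. Onset can fall only on a coarse scan grid, so a responder median can jump by a whole scan interval through one or two patients.

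**The case against.** - **The word responders does not appear in the onset sentence.** This is true. The section assigns further efficacy endpoints to the ITT population and leaves the at-risk set open. Responders-only is an inference, though the natural one: a range needs observed times, and an all-patient median is not reached if fewer than half respond.
- **No biased comparison is planned.** This also stands. No contrast is named for onset, and a median and range that describe responders are not biased. A reader might infer that the plan commits a selection-biased comparison. The text does not support that; the bias would arise only if someone set the two medians against each other as an effect.
- **The response effect can still be derived.** This stands too. The failure rule keeps all patients in the denominator, so the rates respect the randomization, and an unadjusted difference can be computed from them. It would be wrong to say that the response question cannot be answered.
- **The plan sets no overlap rule.** Correct. The overlap example in step 3 shows only that two intervals are no substitute for a contrast. It is not the error rate of anything the plan does.
- **This is a condensed article about lower-tier endpoints.** The Discussion says that the study is powered only for the primary objective, and a fuller document may name a contrast. That keeps the point minor. It does not remove it, because the article states the analysis for both endpoints and what it states does not deliver its own objective.

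**Conclusion.** The point holds as a minor mismatch between objective and analysis. Objective response and time to onset are listed for treatment effects, but the written methods yield no effect estimate for either, unlike the two endpoints treated beside them. The response rates themselves are sound. The onset summary, read as covering responders, is acceptable description but not a measure of effect.

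The size of the problem cannot be fixed from the article, because it gives no response rates and does not define the at-risk set for onset. The illustrations rest on assumed rates and per-scan probabilities and show what can happen, not what will. The primary noninferiority test and the two neutropenia tests are unaffected.

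**What to change.** - **Response:** add a between-arm contrast in the ITT set with a 95% CI. This can be the risk difference, or the OR from the logistic model already planned for the progression-free rates. Adjust for ECOG status and liposarcoma histology where the number of responders allows, and name the unadjusted interval in advance as the fallback.
- **Onset:** add the cumulative incidence of first response from randomization in all ITT patients, with progression or death before response as competing events. Give the between-arm difference with a 95% CI at time points that match the scans. With scans every 6-7 weeks the second is due at weeks 12-14 and the third at weeks 18-21, so weeks 14 and 21 would suit, whereas a reading at week 12 could miss the second scan. State how another anticancer therapy started before response is handled.
- **Description:** keep the median and range, labelled as describing responders only.

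The cost is analysis-plan wording and two standard analyses on data already collected. The downside is wide intervals with few responders: about 28 points in total at an assumed 15% in both arms (-15.4 to +12.3). If only description is wanted, rewording the objective would also remove the mismatch, but it would give up the effect estimate.

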### Interventions

#### Control intervention

Doxorubicin is an anthracycline antibiotic with a mechanism of action aimed at topoisomerase inhibition. Doxorubicin (monotherapy) is administered intravenously every 3 weeks at a dose of 75 mg/m^2^ body surface area for a total of six cycles.

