#### Experimental intervention

Pazopanib is a once-daily, orally administered angiogenesis inhibitor targeting vascular endothelial growth factor (VEGF), platelet-derived growth factor, and c-kit receptors [20]. By inhibiting these receptors, pazopanib may stop or slow the rate of tumor growth and development. Pazopanib is provided as white tablets with two doses at 200 mg and 400 mg. Patients receive a daily dose of 800 mg. Treatment is administered until disease progression, treatment failure, or death due to any cause, whichever occurs first. Pazopanib has been approved by the U.S. Food and Drug Administration, the European Medicines Agency, and other regulatory authorities as a monotherapy for patients with advanced renal cell carcinoma and as second-line therapy for advanced STS.

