Randomization and analysis are stratified for two important prognostic factors: ECOG performance status and liposarcoma histology. It can be assumed that the power is increased by performing stratified analyses [23]. Nonetheless, a limitation of the EPAZ study design is the low power for drawing an overall positive conclusion. Obviously, the aim of the study is to show comparable efficacy accompanied by considerable advantages in terms of safety issues and increased health-related quality of life (HRQoL) as a consequence. However, the study is powered only for the primary objective, because the orphan conditions do not allow us to adequately power the study for the primary as well as the two key secondary endpoints, or even additional secondary objectives. We expect that, on basis of the safety profile of either drug and the continuous evaluation of HRQoL, we will be able to show a clinically meaningful benefit of the given therapy. To our understanding, EPAZ is the first study in STS that weights the quality of PFS and will provide data regarding comorbidities and HRQoL in the elderly population.

Pazopanib is an effective treatment in STS. Its activity in previously treated patients is within the range of contemporary first-line activity of doxorubicin [8, 17]. However, the classes of agents used differ substantially between pazopanib and doxorubicin. While pazopanib is an oral tyrosine kinase inhibitor that inhibits the VEGFR, doxorubicin is a classical chemotherapeutic compound. Hence, its toxicity profile differs substantially. It is not known how continuous exposure with chronic toxicity affects patients in comparison with chemotherapy, with its cyclic treatment and adverse events. The principal applicability to elderly patients has been shown in metastatic renal cancer, a disease whose incidence peaks in the sixth and seventh decades of life [25]. If both noninferiority in efficacy and an improved tolerability of pazopanib (and thus improved quality of life) are verified in our trial, a new first-line treatment strategy for elderly patients with STS may become available.

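### The planned adverse event tables make no allowance for time on treatment, which by design is expected to be about 2.4 to 2.6 times longer on pazopanib than on doxorubicin

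*Protocol article*

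**What the plan says.** The article (Secondary and safety analyses) sets the summary of adverse events (AEs) and serious AEs (SAEs) in one sentence, by arm: "Occurrence and frequency of AEs and serious AEs will be evaluated separately for both treatment groups, and frequency tables and corresponding 95 % CIs will be" (…). It attaches no person-time denominator, time-to-first-event method or common window to these tables.

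Treatment length differs between the arms:
- Study design describes "a 4.5-month period of treatment with doxorubicin (18 weeks) or pazopanib until treatment failure".
- Doxorubicin is given every 3 weeks "for a total of six cycles" (Control intervention).
- For pazopanib, "Treatment is administered until disease progression, treatment failure, or death due to any cause, whichever occurs first" (Experimental intervention).

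Only grade 4 neutropenia and febrile neutropenia are defined as rates over time (Secondary endpoints) and modelled by Poisson regression. Their denominator is follow-up time, not time on drug. On observation, the same section states: "Safety and tolerability will be assessed continuously throughout the course of the study". Study design puts follow-up visits at the same time points in both arms, with an end-of-treatment visit 4 weeks after treatment ends. The article does not give the AE cut-off after the last dose.

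**The concern.** The share of patients with at least one event depends on how toxic a drug is and on how long it is taken. When one arm stops at 18 weeks and the other continues to progression, a difference in that share cannot be assigned to either cause from a frequency table alone. With hazards that persist on drug, the mixing works against pazopanib, and more so the longer pazopanib holds the disease.

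This matters because safety and tolerability are stated objectives. The Discussion also says that the overall conclusion will rest on all benefits and risks observed, and it raises the question itself: "It is not known how continuous exposure with chronic toxicity affects patients in comparison with chemotherapy, with its cyclic treatment and adverse events". Frequency tables on their own do not separate chronic from cyclic toxicity.

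**Working it through.** **The plan's own figures.** The article gives no figure for exposure or AE frequency. Its power statement can be used to check that the PFS and follow-up assumptions are read correctly.
- Inputs (Sample size considerations): "For both treatment groups, a median PFS of 6 months is assumed"; accrual 36 months; minimum observation 10 months; allocation 1:2; margin 1.8; one-sided 2.5%.
- Exponential PFS: λ = ln 2 / 6 = 0.1155 per month.
- Event probability with uniform accrual: 1 − (e^(−10λ) − e^(−46λ)) / (36λ) = 0.925.
- 120 patients: 111.1 events; z = √(111.1 × 1/3 × 2/3) × ln 1.8 − 1.96 = 0.96; power 83.1% (stated: above 80%).
- 108 patients (10% lost): 99.9 events, power 79.1% (stated: 79–80%).

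Both reproduce.

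**Time on drug.** Assume that pazopanib runs to progression and doxorubicin to progression or T = 18 weeks = 4.14 months, with no stop for toxicity.
- Doxorubicin patients still progression-free at T: e^(−λT) = 62%.
- Mean on doxorubicin: (1 − e^(−λT)) / λ = 3.29 months.
- Mean on pazopanib: 1/λ = 8.66 months, or 8.66 × 0.925 = 8.01 months with administrative censoring.
- Ratio: 2.63, or 2.43 with censoring. With the article's 4.5 months as T it is 2.47, or 2.28 with censoring as well.
- Other medians, common to both arms: 1.72 at 3.3 months, 2.15 at 4.6, 3.32 at 8.

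**Patients with at least one event.** Assume one constant on-drug hazard μ in both arms.
- Pazopanib: μ / (μ + λ).
- Doxorubicin: [μ / (μ + λ)] × (1 − e^(−(μ+λ)T)).
- Example, μ = 0.10 per month: pazopanib 0.10 / 0.2155 = 46%; doxorubicin 0.464 × (1 − e^(−0.892)) = 27%. At μ = 0.05 the figures are 30% and 15%; at 0.20, 63% and 46%.

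Solving for μ at fixed doxorubicin frequencies:

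| Doxorubicin | μ per month | Pazopanib | Gap (points) | Ratio | Ratio with 4-week post-treatment window |
|---|---|---|---|---|---|
| 5% | 0.016 | 11.9% | 6.9 | 2.39 | 2.11 |
| 10% | 0.032 | 21.8% | 11.8 | 2.18 | 1.98 |
| 20% | 0.069 | 37.4% | 17.4 | 1.87 | 1.75 |
| 34% | 0.131 | 53.2% | 19.2 | 1.56 | 1.51 |
| 50% | 0.225 | 66.1% | 16.1 | 1.32 | 1.31 |
| 70% | 0.422 | 78.5% | 8.5 | 1.12 | 1.14 |
| 90% | 1.109 | 90.6% | 0.6 | 1.01 | 1.02 |

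The table leaves out administrative censoring. In the 5% row it would multiply the pazopanib figure by about 1 − (e^(−1.311) − e^(−6.03)) / (0.1311 × 36) = 0.943, giving 11.2% and a ratio of about 2.25. In the 34% row the change is about 1%.

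If the hazard is zero after week 18, exposure at risk is the same in both arms and the ratio is 1.0. Events per unit of time on drug also give 1.0 under the equal constant hazard.

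**The case against.** The strongest reply is that this is a condensed article with one sentence on AEs, and that exposure-adjusted displays and the AE window are normally left to the full protocol or analysis plan. That stands in part: nobody can say from this text that such displays are absent elsewhere. But the article does state a method, and it gives a time denominator to two toxicities while giving frequency tables to the rest.

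Other points also carry weight:
- The share of patients with an event under each regimen as given is a legitimate measure of treatment burden. Preferring risk per month on drug is a choice of estimand. This stands, and it is why the tables should be kept.
- Safety is observed throughout the study at the same visit times, so events after week 18 may be counted on doxorubicin. A 4-week window alone lowers the ratio at 5% from 2.39 to 2.11. Counting longer would narrow the gap further, but with events off drug or possibly under a later therapy.
- The confirmatory toxicity endpoints already have a time denominator, and the AE tables carry no test or decision rule. With hazards that persist on drug, the distortion runs against pazopanib, so it would not create a false tolerability advantage.
- A rate per patient-month spreads early-onset events over longer pazopanib exposure and can favour pazopanib.

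A reader might infer that two equally toxic drugs would in general show far more patients with events on pazopanib. The documents do not support that. They give no AE hazard, and the gap shrinks or disappears for very common or early events.

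**Conclusion.** The point holds in a limited form. The stated AE and SAE tables take no account of a time on treatment that differs by design, by an expected 2.4- to 2.6-fold (2.3-fold if the 4.5-month cap and administrative censoring are combined). This rests on exponential PFS with a 6-month median in both arms and treatment continued to progression or the six-cycle limit.

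Under the further assumption of one constant on-drug hazard, events at 5 to 34% on doxorubicin would appear in about 1.5 to 2.4 times as large a share of pazopanib patients. The largest gap in the table is about 19 points, at 34%. At 70% the gap is 8.5 points (9.5 with the 4-week window) and at 90% it is 2 points or less. For events confined to the first 18 weeks there is none.

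It would go too far to call the frequency tables wrong or to discard them. They answer a whole-regimen question, but they are a poor sole basis for comparing the drugs' tolerability. The primary and confirmatory analyses are not affected.

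**What to change.** Keep the frequency tables, labelled as whole-regimen burden. For AEs of grade 3 or higher, SAEs and AEs leading to discontinuation, add:

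1. Exposure-adjusted incidence by arm, per patient-month on treatment plus 4 weeks.
2. Cumulative incidence by arm at two common time points: an early one, for example week 22 (18 weeks plus the 4-week end-of-treatment visit), and a later one that takes in the week-26 assessments. Echocardiography is repeated at week 26, so a week-22 cut alone would miss findings first made there and would leave out longer pazopanib exposure.

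State the AE reporting window and a rule for events after the start of other anticancer therapy. Read the between-arm comparison from all the tables together, not from crude proportions alone. If the full protocol or analysis plan already contains these displays, a cross-check is enough.

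The cost is two extra descriptive tables from AE and dosing dates, which the trial can be assumed to hold. Treatment, visits and sample size do not change. The drawback is that the rate per patient-month assumes a roughly constant hazard and dilutes early-onset events on pazopanib, which is why it is paired with cumulative incidence.
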